### Strategies to improve adherence to interventions {11c}

Most of the interventions take place during admission on the PICU by research staff. The respiratory morbidity score questionnaires will be administered electronically by email and reminders will be sent automatically after 1 week.

### Relevant concomitant care permitted or prohibited during the trial {11d}

Standard of care is provided for all enrolled patients. It is guided by clinical judgement, local guidelines, and international recommendations from PALICC and PEMVECC, and includes ventilator management, sedation and analgesia use, nutrition, transfusion management and hemodynamic and fluid management [17, 25]. Ventilator management goals are adequate oxygenation and ventilation, defined by pulse oximetry oxygen saturation (SpO_2_) 88–92% and 7.20 ≤ pH ≤ 7.35 (irrespective of PaCO_2_) during the acute phase of disease. PALICC recommendations include expiratory tidal volume (Vte) 5–7 ml/kg ideal body weight (IBW), peak inspiratory pressure (PIP) ≤ 28 cm H_2_O (may allow up to 32 cm H_2_O for patients with poor chest wall compliance, i.e. those with increased chest wall stiffness or increased abdominal pressure) and PEEP set by FiO_2_ and respiratory system mechanics. Use of pulmonary specific and non-specific ancillary treatment including inhaled nitric oxide (iNO), steroids, surfactant and prone positioning are also at the discretion of the local bedside team. Use of escalating interventions such as high-frequency oscilattory ventilation (HFOV) or ECLS is also at the discretion of the bedside team. Ventilation treatment failure is defined as a 4-h pattern of either persistent hypoxia (SaO_2_< 85%) with FiO_2_ 1.0 and max PEEP or persistent hypoventilation (pH < 7.20) with PIP > 35 cmH_2_O and a respiratory rate that does not cause intrinsic PEEP. Onset of weaning is at the discretion of the attending physician. Once deemed eligible for weaning, a daily extubation readiness test (ERT) is performed per institutional algorithm.

Patients will be managed using a conservative fluid strategy. The goal is adequate cardiac output to meet the metabolic needs of the patient, specifically, a normal blood pressure for age, brisk capillary refill, and adequate peripheral perfusion to achieve adequate end organ perfusion. The care team will delineate daily mean arterial blood pressure goals. Hemodynamic management may be guided by devices such as pulse contour cardiac output (PiCCO). Diuretic therapy is used to achieve desired fluid balance. Type of drug, starting and maintenance dose is at the discretion of the local care team, taking the goals of fluid management into account. Use of vaso-active medications is also at the discretion of the care team. Maintenance fluids are calculated per standard paediatric practice according to local guidelines. The care team will determine the type of fluid (colloids, crystalloids) administered. All fluids, including IV continuous infusions, IV intermittent medications, blood products, IV and enteral nutrition, will contribute to the patient’s hourly total. Medications should be administered using the least amount of fluid possible.

Patient’s level of comfort is assessed per phase of illness and criticality at least every 4 h while intubated. The Comfort B score is used per discretion of the local care team in all patients, although it must be noted that it cannot be used in paralysed patients [26]. In all patients, patient comfort is also deemed insufficient if there is a persistent > 20% increase in heart rate and blood pressure either spontaneously or with stimulation despite managing obvious causes for discomfort such as (partial) endotracheal tube blockage, mucus retention or constipation. If present, sedation and/or analgesia regimens can be modified according to local guidelines. Centres may substitute drugs within a class (e.g. narcotics - morphine or fentanyl or benzodiazepines - midazolam and lorazepam) and by route of administration (e.g. enteral for intravenous). Alternative measures such as the analgesia nociception index (ANI) require additional monitoring devices that are not available in all participating centres. Local screening tools for withdrawal and/or delirium will be used.

### Provisions for post-trial care {30}

A participant insurance by the UMCG covers all participants who suffer harm from trial participation with a maximum of €650.000 per subject, €5.000.000 max per study and €7.500.000 per year.

### Outcomes {12}

#### Primary outcome measure

Cumulative respiratory morbidity score 12 months after PICU discharge, adjusted for confounding by age, gestational age, family history of asthma and/or allergy, season in which questionnaire was filled out, day-care and parental smoking.

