## Background and rationale {6a}

Paediatric acute respiratory distress syndrome (PARDS) is a manifestation of severe, life-threatening lung injury. The prevalence of PARDS in critically ill, mechanically ventilated children may be as high as 10% of all children admitted to the paediatric intensive care unit (PICU) with mortality rates ranging up to 40–50% [1]. The disease is characterised by massive pulmonary inflammation, alterations in surfactant homeostasis and ventilation/perfusion mismatching leading to severe hypoxemia and multiple organ dysfunction [2]. Mechanical ventilation (MV) has added significantly to the survival of PARDS patients but also induces a pulmonary inflammation (biotrauma) that aggravates pre-existing lung injury (double-hit), a concept known as ventilator-induced lung injury (VILI) [3–5].

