Critical care practitioners have adopted the philosophy of maintaining spontaneous breathing in mechanically ventilated patients as much as possible. However, a study in adults with severe ARDS challenged these practices. Early use of neuromuscular blocking agents (NMBAs) in adults with severe ARDS, defined as PaO_2_/FiO_2_ ratio less than 150 mmHg, resulted in improved 90-day survival and increased time off the ventilator without increasing muscle weakness [6]. In this study, 340 patients with early severe ARDS, meeting criteria within 48 h of ICU admission, were randomised to cisatracurium besylate or placebo once adequately sedated. After adjustment for baseline PaO_2_/FiO_2_, plateau pressure and the Simplified Acute Physiology Score, the cisatracurium group had a hazard ratio for death at 90 days of 0.68, (95% confidence interval [CI], 0.48 to 0.98; *P* = 0.04), compared to the placebo group. These findings remained consistent when combined in a meta-analysis with earlier, smaller studies from the same group of investigators [7]. Additional beneficial effects of NMBAs observed included sustained improvement in oxygenation, less organ dysfunction, and a lower pro-inflammatory response [8–10]. However, the practice change that followed this trial came under scrutiny after the publication of the Re-evaluation Of Systemic Early Neuromuscular Blockade (ROSE) trial in 2019 [11]. This trial was designed to determine the safety and efficacy of early NMBAs with concomitant heavy sedation as compared with a strategy of usual care with lighter sedation targets. It was prematurely terminated for futility after the inclusion of 1006 patients because no difference in 90-day survival (42·5% vs 42·8%) was found.

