## Data collection and management and storage of biological specimens

### Plans for assessment and collection of outcomes {18a}

#### Primary outcome

The respiratory morbidity will be assessed using a structured questionnaire in agreement with recommendations from the American Thoracic Society [29]. This parental questionnaire studies the presence of respiratory symptoms including cough, wheezing and shortness of breath during rest and/or activity. The questionnaire consists of 14 items that can only be answered by yes or no. The questionnaire is commonly used and validity of the items in the respiratory morbidity score has been shown [29, 30]. Upon discharge, parents or legal caretakers are asked for their e-mail address and phone number; the personalised link to the web-based questionnaire will be e-mailed to them 12 months after PICU discharge. If there is no response within 7 days, they will receive a reminder via e-mail. The questionnaire is personalised and anonymised. The same questionnaire is used upon PICU admission to study baseline respiratory morbidity.

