## Statistical methods

### Statistical methods for primary and secondary outcomes {20a}

Data is analysed with an intention-to-treat approach. The primary outcome measure is a continuous outcome parameter. First, it will be tested for normality using the Shapiro-Wilk test. Dependent upon the outcome of this test, in the univariate analysis, the primary outcome will be displayed as mean ± standard deviation or median (25–75 interquartile range) and analysed using either the Student *t* test or the Mann-Whitney *U* test. Paired analysis will be used to compare the primary outcome with its baseline value. In multivariate analysis, zero inflated regression analysis is used to adjust for possible confounding by age, gestational age, family history of asthma and/or allergy, season in which questionnaire was filled out, parental smoking, and parental perception of the outcome of randomisation. Depending on the outcome of the analysis on randomisation outcome, variables that were significantly different between the intervention and control arm will also be adjusted for in the multivariate analysis. On top of that, we will adjust if there is an imbalance in the use of (non-) pulmonary specific ancillary treatment used during PICU admission.

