### Methods in analysis to handle protocol non-adherence and any statistical methods to handle missing data {20c}

All study participants who have received a dose of the study drug will be included in a modified intention to treat analysis. Participants who have received the study drug during 48 h and with a respiratory morbidity score 12 months after discharge (primary outcome measure) will be included in the per-protocol population.

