## Discussion

This is the first paediatric trial evaluating the effects of muscular paralysis in moderate-to-severe PARDS. The proposed study addresses a huge research gap identified by PALICC by evaluating a practical need regarding the treatment of PARDS [39]. Paediatric critical care practitioners are inclined to use interventions such as NMBAs in the most critically ill. Data from the Paediatric ARDS International Epidemiology (PARDIE) study showed that approximately one of every three mechanically ventilated PICU patients received continuous NMBAs [13]. The use of NMBAs increased with PARDS severity and was more common among patients who also received inhaled nitric oxide (iNO) and HFOV. However, this liberal use of NMBAs must be weighed against potential side-effects, with CIPNM being the most prominent, a phenomenon that has been observed especially in adults who are on concurrent corticosteroids or have renal failure [19, 20]. The proposed study will provide much needed scientific support in the decision-making to start NMBAs in moderate-to-severe PARDS.

The primary outcome of this proposed study is a functional one, measured during follow-up. We choose this outcome for two reasons. First, based on the relatively low but highly variable PARDS mortality rates, the proposed study would require a large sample size. Consequently, such a study would have to run for many years, thereby potentially making the study not only not feasible but also creating the risk of the research question becoming less important [1]. Second, the focus in paediatric critical care research is redirecting towards functional outcomes [40, 41]. We think that this makes our primary outcome measure highly relevant. The maximum level of pulmonary function reached during childhood is a crucial determinant for respiratory function in adults [42–45]. Any event that causes lung injury and thereby reduces the level of pulmonary function may thus exert a negative impact on later life. This may especially be true for lung injurious events during early childhood (i.e., children < 8 years of age) when the lung is still developing. MV needs to be considered such an event in our perspective, which makes pulmonary function an important outcome measure.

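### The primary score exists only for children alive at 12 months, so the comparison labelled intention-to-treat is a comparison among survivors and is biased if rocuronium changes mortality

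*Protocol article*

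**What the plan says.** The primary outcome (Outcomes {12}) is "Cumulative respiratory morbidity score 12 months after PICU discharge, adjusted for confounding by age" and several further factors. It is obtained from parents about their child's symptoms: under Plans for assessment and collection of outcomes {18a}, "the personalised link to the web-based questionnaire will be e-mailed to them 12 months after PICU discharge".

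On populations, section {20a} states "Data is analysed with an intention-to-treat approach", and section {20c} states "All study participants who have received a dose of the study drug will be included in a modified intention to treat analysis". Section {20c} asks for a 12-month score only for the per-protocol set. Its heading covers missing data, but it gives no rule for a child who died.

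On tests, section {20a} says the score is "analysed using either the Student *t* test or the Mann-Whitney *U* test", depending on a normality test, and then entered in a zero-inflated regression. All three need an observed score.

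Two other places bear on the point:

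- The dropout allowance in Sample size {14} is 20% per group and names only consent withdrawal and loss to follow-up.
- For ventilator-free days, an exploratory outcome, section {18a} does score death: patients who die before day 28 without having stayed extubated for more than 24 h receive zero. Mortality itself is exploratory and is defined as PICU mortality and mortality to 90 days after PICU discharge.

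**The concern.** A child who dies in the PICU or in the following year belongs to the intention-to-treat set and to the modified set, but has no value in any stated primary test. What remains is a comparison of survivors. Randomisation balances the arms at entry; it does not balance those who survive if treatment affects who survives.

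The direction depends on the effect. If rocuronium saves some of the sickest children, they probably bring high scores into its arm and make it look worse. If it costs the lives of such children, its remaining patients look healthier.

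The article gives reason to take this seriously. Its background gives PARDS "with mortality rates ranging up to 40–50" per cent, and describes an adult trial in which the group given a neuromuscular blocker "had a hazard ratio for death at 90 days of 0.68". The interim rule also stops the trial for futility when the primary outcome shows no difference, so a survivor effect could influence that decision too.

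**Working it through.** **Inputs from the article.** 74 evaluable and 89 enrolled per arm; alpha 5% (taken as two-sided); power 80%; 20% dropout; adult hazard ratio 0.68; mortality up to 40–50%.

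**Assumptions, because the article gives no figure.** 12-month mortality in each arm; the correlation ρ between a child's tendency to die and the later morbidity score, taken as 0.3 to 0.7; the spread of the score.

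**Step 1: design effect.** No mean or SD is given, so the planned effect can only be back-solved: d = (1.960 + 0.842) / √(74/2) = 0.461 SD.

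**Step 2: mortality scenarios.** Applying the adult hazard ratio to control survival gives 0.80^0.68 = 0.859 (mortality 14.1%) and 0.60^0.68 = 0.707 (29.3%). Read instead as a risk ratio, 0.68 × 40% = 27.2%.

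**Step 3: bias with no true effect on morbidity.** Let morbidity and death propensity be bivariate normal, with mortality m and cut-off c = Φ⁻¹(1 − m). The survivors' mean is shifted by −ρ·φ(c)/(1 − m). The bias is the difference between arms, positive meaning against rocuronium.

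- 20%: 0.2800/0.80 = 0.3500. 14%: 0.2226/0.86 = 0.2588. Difference 0.0912; times ρ, 0.027 to 0.064 SD.
- 40%: 0.3863/0.60 = 0.6439. 27%: 0.3306/0.73 = 0.4529. Difference 0.1910; times ρ, 0.057 to 0.134 SD.

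**Step 4: effect on the test.** Evaluable children per arm = 89 × 0.8 × (1 − m), and SE = √(1/n_C + 1/n_T), with the SD held at 1. For 20% versus 14%, n = 57.0 and 61.2, SE 0.184. For 40% versus 27%, n = 42.7 and 52.0, SE 0.207.

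| Mortality, control v active | Bias (SD) | Share of 0.461 | Two-sided type I error |
|---|---|---|---|
| 10% v 5% | 0.03–0.06 | 6–13% | 5.3–6.4% |
| 20% v 14% | 0.03–0.06 | 6–14% | 5.3–6.4% |
| 40% v 29.3% | 0.05–0.11 | 10–24% | 5.6–8.3% |
| 40% v 27% | 0.06–0.13 | 12–29% | 5.9–9.9% |
| Equal, same kind of child dying | 0 | 0 | 5% |

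Swapping the arms reverses the sign. With 14% mortality on control and 20% on rocuronium, the chance of a false significant benefit rises from 2.5% to 3.5–5.3%.

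**Step 5: would ranking death worst serve as the primary test?** Simulation with 89 per arm, 20% loss among survivors, true effect 0.461 SD, equal mortality, and ρ of 0 and 0.5 (6,000 trials each) gives this Mann-Whitney power:

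| Mortality in both arms | Survivors only | Death ranked worst |
|---|---|---|
| 10% | 72–74% | 55–57% |
| 20% | 66–71% | 35–39% |
| 40% | 54–59% | 14–16% |

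**Step 6: cost of requiring only agreement in direction.** In the same setting, when the survivor comparison (t test) shows a significant benefit, the worst-rank comparison points the same way in over 99% of trials at 10% mortality, about 99% at 20% and about 89% at 40%.

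**The case against.** The strongest reply is that an effect on survival is not established. The first adult trial used a different blocker. The later and larger one, described in the same background section, stopped for futility with 42.5% against 42.8% at 90 days. The Discussion justifies the functional outcome "based on the relatively low but highly variable PARDS mortality rates", so the 40–50% is an upper limit and not an expectation. With equal mortality and the same kind of child dying, the bias is zero. This stands, and it limits the size; it does not make a survivor comparison an intention-to-treat one.

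A second reply is that the analysis plan, not shown, may deal with deaths. It may add sensitivity analyses. But the article itself fixes the outcome, populations and tests, has a section headed for missing data, and scores death for a lesser outcome. As fixed, those elements leave deaths out.

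A third is that the functional outcome was chosen deliberately, and that ranking death worst asks another question at a heavy price in power. Step 5 bears this out.

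A reader might also infer that a significant benefit could be produced by excess deaths alone. The documents do not support that. Nothing in them suggests higher mortality on rocuronium, and in the reversed scenario the risk of a false benefit rises but stays near 5% or below. Deaths would also be visible: mortality is reported, death is a serious adverse event, and a monitoring board reviews the trial.

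**Conclusion.** The concern holds in this conditional form. The primary comparison is among survivors, and calling it intention-to-treat is not accurate. It is biased if rocuronium changes mortality, in the direction opposite to its effect on survival, provided the children most likely to die would also have had the worse scores.

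The size cannot be fixed from the documents. Under the assumptions above the bias is 0.03 to 0.13 SD, or 6 to 29% of the design effect, with modest inflation of type I error. The upper end needs both mortality near 40% and a full carry-over of the adult survival benefit to 12 months. This is a should-fix: it limits what may be concluded from the score, but it does not invalidate the trial or require a different primary outcome.

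**What to change.** 1. Keep the adjusted score as primary, but describe it as a comparison among survivors and not as intention-to-treat.
2. Report deaths from randomisation to 12 months after PICU discharge by arm, next to the primary result.
3. Prespecify, before unblinding, one key sensitivity analysis: a Mann-Whitney comparison in which death before the 12-month questionnaire takes the worst rank. Require it to agree in direction before superiority is claimed.

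Worst rank should not replace the primary analysis, because of the loss of power in step 5. As a direction check it costs little at low or moderate mortality; near 40% it would withhold about one in nine otherwise significant results when mortality is truly equal.

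The cost is analysis-plan wording, one extra analysis, and a rank result that mixes survival with morbidity, so both components must be shown. Vital status at 12 months must also be confirmed for every child: the mortality outcome runs only to 90 days after discharge, and a later death could otherwise be recorded as an unanswered questionnaire. Surviving children who withdraw or are lost still have no score under this change and need their own missing-data rule.

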#### Secondary outcome measures

Secondary outcomes include LCI and FRC measured using multiple breath wash-out 12 months after PICU discharge, and the level and time course of the cumulative respiratory morbidity score assessed at baseline, 3, 6 and 9 months after PICU discharge. Secondary outcome measures related to the acute phase of disease (i.e., during PICU admission) include level and time course of ventilator settings (peak inspiratory pressure, plateau pressure, mean airway pressure, driving pressure, PEEP, set rate, total rate, inspiratory time), respiratory system mechanics (quasistatic compliance, dynamic compliance, respiratory system resistance), metrics of oxygenation (SpO_2_/FiO_2_ ratio, PaO_2_/FiO_2_ ratio, OI, OSI) and ventilation (PCO_2_, pH), and hemodynamic parameters (heart rate, blood pressure, central venous pressure, daily cumulative fluid balance, number of fluid challenges). We will measure the level and time course of the non-respiratory pediatric logistic organ dysfunction 2 (PELOD – 2) score as measure of organ dysfunction and pediatric Risk, Injury, Failure, End-stage renal failure (pRIFLE) criteria for acute kidney injury, the number of adverse drug reactions, and re-intubations [27, 28]. We will study the level and time course of the pulmonary and systemic inflammatory response, the prevalence of critical illness polyneuropathy and myopathy, and ventilator-associated pneumonia.

##### Exploratory outcome measures

These include use of (non-) pulmonary ancillary treatment (e.g. steroids, inhaled drugs, prone positioning) and HFOV, daily cumulative dosage sedatives and analgesics, prevalence of drug withdrawal symptoms and delirium, ventilator-free days at day 28 (VFD), length of MV, length of PICU stay and mortality. We will also explore changes in Pediatric Cerebral Performance Category and Pediatric Outcome Performance Category.

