## Abstract

**Background:**

Paediatric acute respiratory distress syndrome (PARDS) is a manifestation of severe, life-threatening lung injury necessitating mechanical ventilation with mortality rates ranging up to 40–50%. Neuromuscular blockade agents (NMBAs) may be considered to prevent patient self-inflicted lung injury in PARDS patients, but two trials in adults with severe ARDS yielded conflicting results. To date, randomised controlled trials (RCT) examining the effectiveness and efficacy of NMBAs for PARDS are lacking. We hypothesise that using NMBAs for 48 h in paediatric patients younger than 5 years of age with early moderate-to-severe PARDS will lead to at least a 20% reduction in cumulative respiratory morbidity score 12 months after discharge from the paediatric intensive care unit (PICU).

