**Methods:**

This is a phase IV, multicentre, randomised, double-blind, placebo-controlled trial performed in level-3 PICUs in the Netherlands. Eligible for inclusion are children younger than 5 years of age requiring invasive mechanical ventilation with positive end-expiratory pressure (PEEP) ≥ 5 cm H_2_O for moderate-to-severe PARDS occurring within the first 96 h of PICU admission. Patients are randomised to continuous infusion of rocuronium bromide or placebo for 48 h. The primary endpoint is the cumulative respiratory morbidity score 12 months after PICU discharge, adjusted for confounding by age, gestational age, family history of asthma and/or allergy, season in which questionnaire was filled out, day-care and parental smoking. Secondary outcomes include respiratory mechanics, oxygenation and ventilation metrics, pulmonary and systemic inflammation markers, prevalence of critical illness polyneuropathy and myopathy and metrics for patient outcome including ventilator free days at day 28, length of PICU and hospital stay, and mortality

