### Objectives {7}

The primary objective is to test the hypothesis that the use of NMBAs for 48 h in paediatric patients younger than 5 years of age with early moderate-to-severe PARDS will lead to at least a 20% reduction in cumulative respiratory morbidity score 12 months after discharge from the PICU.

The secondary objectives are to evaluate the effects of NMBAs on pulmonary and systemic inflammation, metrics for oxygenation and ventilation, non-respiratory organ dysfunction, and respiratory system mechanics.

Exploratory objectives: ventilator free days (VFD) at day 28, PICU and hospital length of stay, 90-day mortality, concomitant use of sedatives, complications (e.g. adverse drug reactions, reintubation rate, critical illness polyneuropathy and myopathy, ventilator-associated pneumonia (VAP), withdrawal syndrome, delirium), the course of the respiratory morbidity score at 3, 6 and 9 months and lung function (lung clearance index (LCI), functional residual capacity (FRC).

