#### Secondary outcomes

For the secondary outcome measures, repeated measures will be tested using generalised estimating equations (GEE), adjusting for the outcome of randomisation and time and any other confounding factors applicable to the outcome measure. Non-repeated continuous measures will be compared between using either the Student *t* test or the Mann-Whitney *U* test, non-repeated dichotomous variables will be tested using the Chi-squared test or the Fisher Exact test if the absolute value is below 5. They will be displayed as a percentage (%) of the total with a 95% confidence interval.

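### Length of ventilation, PICU stay and hospital stay have no rule for death, so a mortality difference can distort their plain two-group comparison, in a direction set by when deaths occur

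*Protocol article*

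**What the plan says.** All references are to the protocol article.

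- **Which outcomes.** Outcomes {12}, exploratory outcome measures, lists "ventilator-free days at day 28 (VFD), length of MV, length of PICU stay and mortality". Hospital stay is not in that list. It is an exploratory objective in Objectives {7} ("PICU and hospital length of stay, 90-day mortality"), and the abstract's Methods puts "ventilator free days at day 28, length of PICU and hospital stay, and mortality" under secondary outcomes.
- **Which test.** Statistical methods {20a}, under the heading for secondary outcomes: "Non-repeated continuous measures will be compared between using either the Student" t test or the Mann-Whitney U test. No separate method is given for exploratory outcomes.
- **Which children.** {20a} states "Data is analysed with an intention-to-treat approach". Section {20c} states "All study participants who have received a dose of the study drug will be included in a modified intention to treat analysis". Neither limits the durations to survivors.
- **How death is handled.** Section {18a} sets ventilator-free days to 0 for a child who dies before day 28 without having stayed extubated for more than 24 hours. No such rule is given for length of ventilation or of stay. Mortality is a separate outcome.
- **How much mortality.** The abstract's Background cites "mortality rates ranging up to 40–50" per cent. The Discussion calls PARDS mortality relatively low but highly variable.

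**The concern.** A stay ends in discharge or in death, and a period of ventilation ends in extubation or in death on the ventilator. If both endings are entered as a number of days, a child who dies on day 4 contributes a shorter, apparently better value than a survivor discharged on day 10. The same child, if still ventilated, has the worst possible ventilator-free-days value, 0. Two outcomes named in one sentence can then point in opposite directions because of the same deaths.

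At stake is the reading of measures that the abstract presents as patient outcomes. A difference in stay could reflect who died and when, rather than how fast children recovered.

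**Working it through.** The protocol gives no figure for length of ventilation or stay, so there is nothing to reproduce. The check asks how far the stated comparison moves when the drug changes mortality only.

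**Inputs.** From the protocol: 89 per arm and alpha 5% (Sample size {14}; two-sided is assumed). Assumed, because the protocol gives no values: stay in survivors lognormal, median 12 days, log-SD 0.7; time to death lognormal, median *d* days, log-SD 0.8; mortality 20% v 10% or 40% v 25% (placebo v rocuronium). The drug has no effect on survivors' stay, and children saved stay as long as other survivors.

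**Step 1: direction.** Let *q* be the probability that a random survivor's stay exceeds a random time to death, and m_P and m_R the mortality on placebo and rocuronium. Adding the four kinds of pair (both survive, both die, one of each in either order) gives the quantity that the Mann-Whitney test examines:

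P(duration on rocuronium > duration on placebo) = 0.5 + (m_P − m_R)(q − 0.5), with q = Φ( ln(12/d) / √(0.7² + 0.8²) ) = Φ( ln(12/d) / 1.063 ).

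For d = 5: q = Φ(0.8755/1.063) = 0.795. At 20% v 10%: 0.5 + 0.10 × 0.295 = 0.530. The result is exactly 0.5 if mortality is equal or if q = 0.5 (d = 12), and it falls below 0.5 when deaths are late.

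**Step 2: size.** Simulation of 4,000 trials per row. The shift is rocuronium minus placebo in median duration. The last column is the share of trials with Mann-Whitney p < 0.05 and longer stay on rocuronium; chance gives about 2.5%.

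| Mortality | Death median (d) | q | P(longer on rocuronium) | Shift (d) | Significantly longer |
|---|---|---|---|---|---|
| 20% v 10% | 4 | 0.849 | 0.535 | +0.93 | 12.0% |
| | 5 | 0.795 | 0.530 | +0.79 | 9.6% |
| | 6 | 0.743 | 0.524 | +0.69 | 8.0% |
| | 12 | 0.500 | 0.500 | 0.0 | 2.2% |
| | 18 | 0.351 | 0.485 | −0.46 | 1.0% |
| 40% v 25% | 4 | 0.849 | 0.552 | +1.50 | 22.8% |
| | 5 | 0.795 | 0.544 | +1.24 | 17.6% |
| | 6 | 0.743 | 0.536 | +1.04 | 13.6% |
| | 12 | 0.500 | 0.500 | 0.0 | 2.2% |
| | 18 | 0.351 | 0.478 | −0.83 | 0.7% |

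**Step 3: smaller mortality effects.** A second set of assumptions uses survivors at median 10 days, log-SD 0.6 throughout, and a relative risk of death of 0.68. That value borrows the adult hazard ratio in Background {6a} for illustration only. Children saved stay a median of 10 or 14 days; each range spans the two (2,000 trials per scenario).

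- 20% v 13.6% (0.20 × 0.68), deaths at median 4 days: mean shift +0.5 to +0.75 days, significantly longer in 8% to 11% of trials. Deaths at 15 days: −0.4 to −0.05 days.
- 10% v 6.8% (0.10 × 0.68), deaths at 4 days: +0.2 to +0.4 days, about 5% of trials.
- 40% v 27.2% (0.40 × 0.68), deaths at 10 days: no shift if children saved stay 10 days, +0.6 days if they stay 14. In the 14-day case a survivors-only comparison also shifts, by +0.85 days.

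**The case against.** **The test is inferred.** The t/Mann-Whitney sentence is about secondary outcomes, and the body of the article calls these durations exploratory. A reader might infer that the protocol scores death as a favourable result. It does not say so; it is silent on how a death enters these durations. This stands as a limit on the claim. But no other test is stated, the abstract does call PICU and hospital stay secondary, and nothing restricts the population to survivors.

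**It could be left to the SAP.** A death rule for an exploratory duration is often SAP detail. This has some force. The point goes beyond an omission only because a test is named, and because the article sets a death rule for ventilator-free days but not for the ventilation length beside it.

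**The direction is not fixed.** A reader might infer that a drug that saves lives will look as if it prolongs stay. The documents do not support that: they give no times of death, and the working shows zero or reversed shifts for later deaths. Nor is a mortality difference assured. Background {6a} cites one adult trial with a hazard ratio of 0.68 and a larger one with 42.5% v 42.8% survival. With equal mortality the formula gives no shift.

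**Other outcomes protect the reader.** Ventilator-free days with death set to 0, and mortality itself, will be reported alongside. This stands, and it limits the harm.

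**Conclusion.** The concern holds in conditional form. As written, the only comparison available for length of ventilation, PICU stay and hospital stay has no rule for death, and its result depends on the mortality difference and on when deaths occur. With 89 per arm, survivors at a median of 12 days and deaths at 4 to 6 days, the spurious prolongation of stay is about 0.7 to 0.9 days at mortality 20% v 10%, and 1.0 to 1.5 days at 40% v 25%. It is absent when deaths fall at about the survivors' median and children saved stay no longer than other survivors. It reverses when deaths are late, and it is small when mortality is near 10%.

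Stay lengths, times of death and mortality effects are assumptions. The stay simulation also only approximates length of ventilation, which is cut short only by death on the ventilator. The measures are exploratory in the body text, and the primary outcome and the sample size are untouched. This is a worthwhile correction of modest weight.

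**What to change.** State that length of ventilation, PICU stay and hospital stay will be analysed as time from randomisation to extubation alive or discharge alive, with death as a competing event: cumulative incidence curves with Gray's test or a subdistribution hazard ratio. Read them beside mortality, since cumulative incidence also responds to it. Give durations in survivors and in non-survivors as description only, because survivors are selected after randomisation.

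Ranking deaths worst is an alternative but not an equivalent, because it is a composite that includes mortality. Under the 12-day model with deaths at about 5 days, it declares benefit in about 21% of trials at mortality 20% v 10% with no effect on stay. With mortality 20% in both arms and stay truly 20% shorter, it has less power than the plain test (27% v 35%). It should not be presented as a power gain.

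The cost is one or two sentences and no data beyond the dates and vital status that the listed outcomes already require. The small downside is that a cumulative incidence is less familiar than a difference in days.
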